### BTB Intervention

Up to 10 one hour sessions occur over 4 months. A home visit can be replaced with check-in telephone calls once steady progress is demonstrated. Sessions integrate five treatment components previously shown to be effective and modified in BTB to resonate with cultural preferences: case management, referral and linkage, depression education, stress reduction techniques, and behavioral activation. (Table 2) Critical is tailoring to participants' depression knowledge level, care management needs, and self-identified goals and behavioral activation plans.

**Table 2 T2:** Intervention Component, Content, and Modification for Target Population

Component	Content	Modifications for Target Population
Education [14,25]	Education provides foundation for introducing other elements of the intervention. It enhances readiness of individuals to address emotion-laden concerns. Specifically, education was provided on: 1) depressive symptoms, 2) how to talk to doctor about symptoms; and 3) relationship of depression to activity and negative cycle of disengagement	1) Used participant's words and own labeling to describe feelings (e.g., "I am feeling blue"). 2) With rapport and only over time, feelings are then labeled as symptoms of "depression." 3) Discussed how to talk to a doctor of a different race. 4) Withdrawal of activity related to specific activities person identified as valued. 5) Used visual mood rating scales and calendars with big print to minimize vision and literacy challenges.
Care management [12,14]	Care management has been found to be more effective than therapy or medication alone for low income elders for whom financial, functional disability and lack of social resources may contribute to depressive symptoms. Specifically this involved: 1) assessment 2) coordination with other services/care management; 3) problem identification and resolution	1) Considered a wide range of care needs most relevant to this population including home repairs, financial concerns, home and neighborhood safety, family conflict. 2) Housing and neighborhood difficulties were evaluated to determine whether person could remain in setting.
Referral and linkage [14,25]	Referrals and linkages are derived from the care management assessment and may include: 1) physician referral for medication review and management; 2) link to psychiatric/psychological follow-up; 3) link to physician for chronic disease management; 4) referral and linkage to other services (e.g., home repairs, financial or legal advisors)	1) Referrals made to vetted community-based service providers sensitive to participants' resources and cultural preferences. 2) For individuals identified as in need of more mental health support, helped make bridge to these services
Stress reduction	Provides immediate, easy-to-learn technique to reduce stress of person and introduce relationship of action and mood change. Specific techniques included: 1) deep breathing; 2) counting; 3) use of music of personal interest	1) Recognition of importance of spirituality and possible objection to meditation as a stress reduction activity. 2) Use of relaxation CD/Tape with participants who did not want to participate in deep breathing exercise.
Behavioral Activation [14,16,25]	Approach is designed to increase frequency of pleasant events and provide positive reinforcement. Self-identification of goals/action plan promotes activation. The approach involves: 1) identification of valued activities and goals; 2) establishment of plan of action for goal attainment; 3) monitoring and adjustment of plan/goals; and 4) identification of new goals and steps to attain them and reinforcement and validation.	1) Awareness and identification of appropriate community-based programs and services that could help participants link to meaningful activities. 2) Use of "Pro/Con" lists and motivational interviewing in formulation of feasible goals. 3) Link individual to senior center to enable continuation of activity participation in a planful, structured setting.

Initial sessions occur weekly and then bi-weekly. In session one, building rapport and a therapeutic relationship begins; also, interventionists assess care management needs and begin education about depressive symptoms making connections between behavior and mood. Explained is that with depression, activities once pleasurable are often stopped which may heighten symptomatology. Likewise, previously pleasurable activities may no longer be pleasurable. Interventionists also discuss sharing depressive symptoms with physicians (if medication may be necessary or for future consideration) and strategies to use when physicians are of a different race. Interventionists introduce deep breathing as a basic stress reduction technique and help participants identify stressful points in the day for its use. In sessions 2-3, interventionists engage participants in simple problem solving to resolve identified care management needs (medical, housing repairs, relocation needs, social, benefits/entitlements), and works on a care management plan involving coordination, referral and linkages to other services if necessary. Other stress reduction techniques (counting, music) are introduced to provide additional tools. In sessions 4-5, interventionists continue addressing care management needs and introduce behavioral activation. Interventionists review daily routines and help participants select a goal and specific activity to add pleasure and personal satisfaction. Active problem solving and motivational interviewing techniques help participants achieve identified activity goals. Potential barriers in carrying out activities are identified and solutions derived which may also require care management (arranging transportation) to engage in desired activities. Sessions 6-8 involve reinforcement of activity engagement, identification of new activity goals and specific steps to achieve them. In sessions 9-10, interventionists review and reinforce all techniques, help participants identify and use behavioral activation strategies, and obtain closure. Approximately 6-7 sessions are devoted to behavioral activation.

### Wait-list control group

The control group does not receive any study-related contact following the baseline interview. After completion of the 4-month reassessment, participants in this group receive the entire BTB intervention as delivered to the initial treatment group.

### Analytic plan

We based our sample size calculation on the following assumptions: a) one primary outcome (severity of depressive symptoms); b) treatment effect sizes reported in previously published intervention studies testing one or more components of the intervention we employ in BTB (effect sizes range from .70 at 6 months and .35 at 12 months in one trial^16 ^to .40 at 3 and 6 months and .60 at 12 months for another trial^14^); c) ability to detect a medium effect size of Cohen's d = 0.40; and d) type I error rate of .05 for the single primary hypothesis. A larger effect size may not be plausible, whereas a smaller effect size brings us at or near levels where the study could have statistical but not clinical significance. In order for this brief, targeted intervention to be worth implementing in a service context, it must yield more than trivial effects. Since our planned analyses are primarily analysis of covariance, we calculated the power of a two-sample t-test. Because we will use analysis of covariance to adjust for baseline values, we expect to have adequate precision and power. To attain 90% power for a two-sided alternative hypothesis using a t-test to compare the two treatment groups with respect to 4-month values require 172 study participants for an effect size of .40. We planned to recruit an additional 20 participants for a total of 192 participants (96 per group). The additional study participants allowed for a conservative estimated attrition rate of 10%. To obtain the necessary sample size of 172, we needed to enroll 192 study participants. The statistical power for secondary analyses is the same as for the primary; 90% for a 0.40 effect size with 5% two-tailed tests. Although we did not conduct power calculations for exploratory aims, these analyses are important in order to refine research questions and hypotheses worthy of future consideration, refinement of the intervention and its dissemination.

The focus of the primary analysis is to examine the effect of the intervention on symptom severity based on the principle of "intention to treat." That is, all subjects assigned to the initial treatment group will be part of the primary analyses regardless of the actual number of intervention contacts received. This approach tests the effects of the intervention without accounting for the extent to which study participants actually receive the intervention. It effectively penalizes the intervention if subjects are not willing to receive it or if subjects receive different doses or exposure to treatment. We will calculate adjusted mean differences in treatment effects on the outcome measure at 4-months using analysis of covariance. We will include as covariates the baseline value of the outcome measure and the stratification variable (recruitment source). Other background characteristics may also be used as covariates if large or statistically significant differences between initial treatment and wait-list control group participants are found for those variables in analyses conducted prior to any efficacy analyses. Prior to conducting the ANCOVA, we will test the normality assumption for the dependent measure by examining the distribution of the residuals. If the residual distribution is skewed, we will use a transformation of the data.

For purposes of reporting results, we will also compute proportions improved. We will use two definitions of improvement: any reduction in PHQ-9; a reduction sufficient to move the patient at least one severity category lower. Note that we do not have to worry about the no symptom (0-4) at baseline group in this definition, as that group is not eligible. The comparison of treatment to wait-list control will be with odds ratio and 95% confidence intervals. We will also examine clinical significance by conducting subsidiary analyses that examine the proportion of individuals in treatment compared to controls who change diagnostic categories. Finally, in another set of analyses we will incorporate measures of the extent to which treatment has been received to evaluate relationship of dose/intensity to treatment outcome. This is for reporting purposes and we are not powering for these alternative endpoints.

As to our second aim, we seek to evaluate whether participants in the initial treatment group maintain reduced symptom presentation from 4 to 8 months. We view retention as a one-sided concept such that any beneficial effect of the intervention at four months is improved or at least maintained at 8 months. Lack of retention is then considered a non-trivial loss of benefit. In the language of clinical treatment trials, this is a "clinical equivalence" or "non-inferiority" hypothesis. Thus, our analyses for our second aim will focus on estimating the amount of 4-month benefit that is retained at 8 months for the treatment group only. We will use confidence intervals in reporting results in order to understand how much loss of benefit is consistent with the data we obtain. Given that the main outcome measure, PHQ-9, has cut off points related to DSM IV depression conditions (e.g., dysthymia, major depression), we will be able to evaluate loss of benefit and retention of effect within the treatment group based on clinically relevant features.

For exploratory aims, we seek to evaluate the mediational role of behavioral activation. We will use separate regressions in which the first regression will evaluate the relationship between 4 month values of the behavioral activation scale (the mediator) and symptom severity as measured by the PHQ-9 at 4 months. The second regression will evaluate the relationship between group assignment (the independent predictor variable) and symptom severity at 4-months (PHQ-9, the criterion). The third regression will evaluate the relationship of treatment assignment (predictor) to PHQ-9 severity scores (criterion) after entering behavioral activation values (mediator). To evaluate the strength of the mediation effects, we will compute the ratio of the unstandardized betas for treatment assignment (beta from regression III divided by beta from regression II) with values less than 1.00 indicating potential mediation. We will repeat these analyses using 8-month values of the PHQ-9. Another exploratory aim is to evaluate whether the intervention has a differential treatment effect based on a study participant's gender, age, or living arrangement (alone/with others), factors which have been shown to be differentially related to depression. To evaluate differential treatment effects at 4-months, we will use a similar analytic strategy as for the main effect model. ANCOVAs will be used in which the covariates will be the baseline value and specific participant characteristic (e.g., male/female; live with other or alone; age 60-64 versus 75+). We will then add an interaction term of group assignment by participant characteristic.

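### 172 participants do not give 90% power at d = 0.40 with the t-test the article names (the power is 74%), and the baseline correlation of about 0.6 that would make the figure hold for ANCOVA is not stated

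*Protocol article*

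**What the plan says.** The Analytic plan section of the protocol article fixes every input to the calculation:

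- Error rate: "type I error rate of .05 for the single primary hypothesis".
- Power and sidedness: "To attain 90% power for a two-sided alternative hypothesis".
- Target effect: "ability to detect a medium effect size of Cohen's d = 0.40".
- Method: "we calculated the power of a two-sample t-test".
- Result: "using a t-test to compare the two treatment groups with respect to 4-month values require 172 study participants for an effect size of .40".

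For 10% attrition the target is then raised, "for a total of 192 participants (96 per group"). Of effects above the target the section says "A larger effect size may not be plausible"; of smaller ones, that they come close to lacking clinical significance. For the secondary analyses the power is given as "90% for a 0.40 effect size with 5% two-tailed tests".

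The section also says that baseline adjustment by ANCOVA is expected to give adequate precision and power. It gives no correlation between baseline and 4-month scores. The primary analysis described next is an ANCOVA with the baseline value and recruitment source as covariates. The section on recruitment and enrollment outcomes reports 208 participants enrolled.

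**The concern.** All the ingredients of a standard sample-size calculation are given, so the result can be checked directly, and 172 is well below what a t-test needs at d = 0.40.

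The article makes only one power statement for the primary endpoint, and the secondary outcomes inherit it. Anyone who later weighs a non-significant result against a claimed 90% power at 0.40 would be relying on a figure that the named method does not support. Whether the planned analysis has that power depends on a quantity the article leaves out.

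**Working it through.** **Inputs** (all from the Analytic plan, except the 208 from the enrollment section): two-sided alpha 0.05; power 90%; d = 0.40 with SD = 1; equal groups; 172 analysable, so 86 per group; attrition 10%; 208 enrolled.

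**1. Trying to reproduce 172.** Normal approximation, per group: n = 2(1.960 + 1.282)² / d².

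- d = 0.40: 2 × 10.507 / 0.16 = 131.3, so 132 per group and 264 in total.
- Exact noncentral t: 132.3 per group, so 133 per group and 266 in total.

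The stated 172 is not reproduced.

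**2. Other t-test settings at d = 0.40** (total N, exact t):

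| Power | Two-sided | One-sided |
|---|---|---|
| 80% | 200 | 156 |
| 85% | 228 | 182 |
| 90% | 266 | 216 |

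None gives 172. Reading 172 as a per-group number would give 96% power, but the 96 per group at enrolment rules that reading out.

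**3. What 172 does give** (exact t, 86 per group):

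- Power at d = 0.40: 74.2% (74.6% by the normal approximation).
- N for 90% power at d = 0.50: 85.03 per group, so 86 per group and exactly 172. Power there is 90.3%.
- Smallest effect detectable with 90% power: d = 0.497.

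**4. Attrition step.** 172 / 0.9 = 191.1, rounded up to 192. This step is right, so the fault lies in pairing 172 with d = 0.40 and 90%.

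**5. What ANCOVA would need.** Adjusting for a baseline that correlates r with the outcome multiplies the residual variance by 1 − r², so the effective standardised effect is d / √(1 − r²).

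- At r = 0.60: 0.40 / √(1 − 0.36) = 0.40 / 0.80 = 0.50, which reproduces 172.
- Smallest r for 90% power at 172: √(1 − 86/132.3) = 0.59.
- With 208 enrolled less 10%: 208 × 0.9 = 187.2, or 93.6 per group. Smallest r: √(1 − 93.6/132.3) = 0.54.

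**6. Power at d = 0.40 over a range of r.** The range is an assumption, because the article gives no value.

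| r | 172 analysed | about 187 analysed |
|---|---|---|
| unadjusted t-test | 74.2% | 77.7% |
| 0.3 | 78.1% | 81.4% |
| 0.4 | 81.2% | 84.4% |
| 0.5 | 85.4% | 88.2% |
| 0.6 | 90.3% | 92.5% |

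With no attrition at all from 208, the unadjusted t-test would have 82% power.

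**The case against.** The strongest defence is that the primary analysis is ANCOVA, not a t-test. The article mentions ANCOVA immediately before giving the number, and a round correlation of 0.60 reproduces 172 exactly. An ANCOVA adjustment left out when the protocol was condensed fits the text as well as a calculation made at d = 0.50. This stands as far as it goes: where 172 came from is open, and the article does not settle it. It does not make the sentence true, because the number is attributed to a t-test on 4-month values and no correlation is given. The secondary-outcome sentence is harder to defend this way, since it would need a correlation of about 0.59 on each of the six scales in Table 1.

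Three stronger readings are tempting, and the article does not support them:

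- **That the trial has a 26% risk of missing its target effect.** That figure (100% − 74%) belongs to an unadjusted t-test on 172. The planned analysis is ANCOVA and 208 were enrolled.
- **That 90% power needs an effect the article itself calls doubtful.** This too holds only for the unadjusted test. Under ANCOVA, 90% at d = 0.40 is attainable if r is high enough.
- **That the authors will read a null result as ruling out 0.40.** Nothing in the article says so. The caution concerns how the printed 90% could be used.

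**Conclusion.** The power statement is wrong as written, and this follows by arithmetic from the article's own inputs. The gap is 94 analysable participants (266 − 172), or about 16 percentage points of power (90% − 74.2%), for the test named. The same error carries into the secondary-outcome sentence.

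The consequence for the planned analysis is smaller and uncertain. At about 187 analysed, ANCOVA power at d = 0.40 lies between 81.4% and 92.5% for r from 0.3 to 0.6, and it reaches 90% at about r = 0.54. This assumes 10% attrition, equal groups and a linear baseline adjustment, with no credit for the stratification covariate.

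Any translation into PHQ-9 points is illustrative only. The SD of 4.9 in Table 3 comes from the second screen, in a sample restricted to scores of 5 or more, whereas the comparison concerns 4-month scores without that restriction.

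**What to change.** Replace the sample-size sentence with something like: *With an unadjusted two-sided 5% t-test, 172 analysable participants give 74% power for d = 0.40 and 90% for d = 0.50.* Follow it with the power of the planned ANCOVA at 172 and at about 187 analysed. Either state the assumed correlation between baseline and 4-month scores with its basis, or show power over r = 0.3 to 0.6 as in the second table above. If 172 did rest on a correlation of about 0.6, say so and describe the calculation as an ANCOVA calculation.

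Correct the secondary-outcome sentence in the same way, scale by scale, since the correlation will differ between measures. When interpreting a non-significant result, do not cite 90% power at d = 0.40.

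The cost is wording only: no added participants and no change to the analysis. The stated power becomes less favourable.

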### Aims and study hypotheses

Our primary aim is to test the immediate effect of the intervention at 4-months on symptom severity (PHQ-9 severity score) in African American older adults (primary trial outcome; between group comparison). Our hypothesis is that participants in the initial treatment group will report fewer depressive symptoms in comparison to control group participants receiving usual care. We also seek to test the maintenance effect of the intervention at 8-months on depression (within group comparison). Our hypothesis is that participants in the initial treatment group will maintain reduced symptom presentation from 4 to 8 months and the wait-list control group will show similar reductions in depressive symptoms as the initial treatment group (within group comparison).

A secondary aim is to evaluate whether BTB has immediate (4 months) and long-term (8 months) effects on quality of life indicators, functional difficulty, anxiety, and depression education and behavioral activation levels. We expect that the initial treatment group will show improvements in these areas relative to the wait-list control group, that improvements will be maintained at 8 months and that the wait-list control group will demonstrate similar improvements at 8 months following their receipt of the intervention.

Several exploratory aims are also proposed. We will evaluate the mechanism of action, or pathways, by which treatment gains are obtained. Given that behavioral activation represents conceptually the key active ingredient of the proposed intervention, we plan to evaluate its mediational effect. We will also evaluate whether the intervention has a differential treatment effect based on a study participant's gender, age, and living arrangement (alone or with others). Given that previous research suggests that participant characteristics may moderate depressive symptoms and treatment outcomes, these exploratory analyses will provide insight as to whether this particular treatment benefits some groups more than others.

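### The 90% power stated for secondary analyses comes from a two-group test at 4 months and cannot apply to the 8-month maintenance hypotheses

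*Protocol article*

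**What the plan says.** The article derives its sample size under Analytic plan from one calculation: "To attain 90% power for a two-sided alternative hypothesis using a t-test to compare the two treatment groups with respect to 4-month values", which is said to "require 172 study participants for an effect size of .40". The error rate is a "type I error rate of .05 for the single primary hypothesis". Enrolment was then raised for 10% attrition, "for a total of 192 participants (96 per group").

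The next step extends the result: "The statistical power for secondary analyses is the same as for the primary; 90% for a 0.40 effect size with 5% two-tailed tests". The only analyses that this paragraph sets apart, as having no power calculation, are the exploratory aims. The following paragraph adds that the alternative PHQ-9 endpoints are not powered.

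Under Aims and study hypotheses, the secondary aim covers both 4-month and 8-month effects on quality of life, function, anxiety, depression education and activation. One of its expectations is that "improvements will be maintained at 8 months".

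Later in the Analytic plan, retention from 4 to 8 months is described differently: "We view retention as a one-sided concept", and "In the language of clinical treatment trials, this is a 'clinical equivalence' or 'non-inferiority' hypothesis". It is to be estimated in the treatment group only, with confidence intervals showing how much loss the data allow. That paragraph is written around depressive symptoms and the PHQ-9.

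**The concern.** The power sentence names a test (two-tailed, 5%), an effect size (0.40) and a power (90%) for a class of analyses that, on the article's own aims, includes 8-month maintenance. The two questions differ in four ways:

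- **Sample:** two groups totalling 172, against one group of about 86.
- **Variability:** the spread between people at 4 months, against the spread of within-person change from 4 to 8 months.
- **Null hypothesis:** no difference, against a loss at least as large as some limit.
- **Sidedness:** two-sided, against one-sided.

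Power for the second question therefore cannot be taken from the first. At stake is how the 8-month results are read. A reader who believes the trial had 90% power for maintenance will give an imprecise 8-month estimate more weight than it deserves.

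**Working it through.** **Inputs from the article (Analytic plan).** 172 evaluable, so 86 per group; d = 0.40; two-sided 5%; claimed power 90%; 192 enrolled (96 per group); attrition 10%. **Inputs the article does not give, so assumed here.** The 4-to-8-month correlation r, taken as 0.3, 0.5 and 0.7; the loss m to be excluded, in SD units; and the same 10% attrition still holding at 8 months.

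**Step 1. The attrition step.** 172 / 0.90 = 191.1, rounded up to an even 192. This reproduces.

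**Step 2. The primary figure that the sentence carries over.**
- Normal approximation: power = Φ(d·√(n/2) − 1.96) = Φ(0.40 × √43 − 1.96) = Φ(2.623 − 1.960) = Φ(0.663) = 74.6%.
- Exact noncentral t: 74.2%.
- 90% power at d = 0.40 needs 133 per group by the exact t (266 in total).
- 86 per group gives 90.3% at d = 0.50, so 172 is the number for a larger effect than the one stated.
- Adjusting for baseline multiplies the residual variance by (1 − ρ²). To reach 90% at d = 0.40 with 86 per group, ρ must be about √(1 − 86/132) = 0.59. The article gives no such correlation and attributes the 172 to a t-test.

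The 90% therefore does not reproduce for the two-group comparison it was computed for.

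**Step 3. The maintenance question.** One group, paired data, n = 86, true change zero. The SD of change is √(2(1 − r)) in outcome-SD units, and the noncentrality is m·√86 / √(2(1 − r)).

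For m = 0.20 the noncentrality is:
- r = 0.3: 0.20 × 9.274 / 1.183 = 1.568
- r = 0.5: 0.20 × 9.274 / 1.000 = 1.855
- r = 0.7: 0.20 × 9.274 / 0.775 = 2.394

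Power to exclude a loss of m (noncentral t, 85 degrees of freedom):

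| Loss excluded | One-sided level | r = 0.3 | r = 0.5 | r = 0.7 |
|---|---|---|---|---|
| 0.20 SD | 2.5% | 34% | 45% | 66% |
| 0.20 SD | 5% | 46% | 58% | 77% |
| 0.30 SD | 2.5% | 64% | 79% | 94% |
| 0.40 SD | 2.5% | 87% | 96% | 99.7% |

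The loss that can be excluded with 90% power at one-sided 2.5% is 0.42, 0.35 and 0.27 SD for the three correlations.

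**Step 4. The larger enrolment.** 208 were enrolled. With 104 in the group less 10%, about 94, power for the 0.20 SD loss at one-sided 2.5% is 37% to 70%. The picture does not change.

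**The case against.** **Narrower scope.** The power sentence directly follows a calculation for 4-month values, and the general description at the start of Methods/Design places the secondary endpoints in the 4-month two-group comparison, with 8-month evaluation listed separately. On that reading the sentence never meant maintenance. The reading is possible, but the article does not state it. The aims put 8-month effects inside the secondary aim, and neither exemption from power calculation mentions maintenance. The scope should be written down.

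**A stronger reading that fails.** A reader might infer that secondary outcomes will be tested two-tailed for change from 4 to 8 months, and that a non-significant decline will then be called maintenance. The article specifies no such test and no such rule. Its one described retention analysis names non-inferiority and relies on confidence intervals for the loss, which is the right safeguard. That the paragraph is written around the PHQ-9 does not show that another method is intended for the other outcomes; a condensed article may leave that to the full plan.

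**Assumption-driven size.** This stands in part. Neither r nor m is in the article, so there is no single corrected power. Reading 0.20 SD as half the benefit would also be loose: 0.40 is a between-group difference, while change within the treated group may include change unrelated to treatment. The 0.20 SD is therefore only an illustration.

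**Different form of the wait-list hypothesis.** The expectation that wait-list participants show similar gains is not a single-group retention question. The point here is confined to maintenance in the initial treatment group.

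**Conclusion.** The point holds as an error in a stated power figure. The 90% belongs to a two-sided, two-group comparison at 4 months and cannot describe 8-month maintenance, which the plan itself frames as one-sided, non-inferiority and within one group. That conclusion needs no assumed numbers. Its size does: with 86 people, r from 0.3 to 0.7 and no true loss, power to exclude a 0.20 SD loss at one-sided 2.5% is about 34% to 66%. Power approaches or passes 90% across that whole range only when the loss to be excluded is as large as 0.40 SD.

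The figure also fails where its design does fit. For the 4-month between-group secondary comparisons, 172 evaluable at d = 0.40 give about 74% with an unadjusted t-test. Rescoping the sentence without restating the number would leave a wrong figure in place.

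The planned retention analysis is not at fault.

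**What to change.** In the Analytic plan:

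1. Limit the power sentence to the 4-month between-group comparisons of secondary outcomes.
2. Restate its figure there: about 74% for d = 0.40 with 172 evaluable, two-sided 5%, unadjusted t-test. If a higher figure is claimed through baseline adjustment, give the correlation it assumes.
3. State that this figure does not apply to 8-month maintenance.
4. State that the confidence-interval approach described for PHQ-9 retention is also used for maintenance of the secondary outcomes.
5. If a precision figure for maintenance is given, give a range with its assumptions, for example: n = 86, correlation 0.3 to 0.7, power of about 34% to 66% to exclude a 0.20 SD loss at one-sided 2.5%.

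This costs wording only, with no new data or participants. Enrolment is closed, but the article says trial procedures are still in progress and results will be reported later, so the correction can be made before the 8-month findings are interpreted. The downside is that the stated power becomes less favourable.
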